#### Intervention group

The patients in the intervention group receive standard care according to the description above but with the CGA and care intervention in addition. As soon as a patient has been randomized to the intervention group, they are scheduled for an “intervention day”, which takes place on pre-decided dates (once every week). During this day, each patient has an individual meeting with an internal medicine physician with geriatric profiling, a study nurse, a physiotherapist or occupational therapist and a dietician. The team conducting the screenings receives introduction about the intervention and education regarding the CGA concept prior to entering the study, and they are also able to address the local expertise of CGA if questions arise during the evaluations. Each profession evaluates the patient clinically and according to the determined screening tools and issues an individual action plan based on these results (Fig. 1). The recommendations are individually prescribed and based on the health care professional’s evaluations based on the standardized screening, according to the CRF. The instruments used by each profession at different measurement points are stated below (Table 1).

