#### Control group

The patients in the control group are assessed using some of the instruments that are used for the intervention group. These measurements are conducted by the regular ward staff (in general a nurse working at the surgery ward/outpatient clinic) at admission to hospital prior to surgery and at the postoperative outpatient visit (Table 2). These extra measurements are the only differences between the control group and patients not included in the trial treated according to standard protocol.

**Table 2 Tab2:** Screening instruments used for the control group, at baseline, at post-op visit (approximately 2 months post-op) and at 12 months post-op

Health care professional	Outcome and instruments	Time of measurements
Ward nurse/nurse at the outpatient clinic	- **Frailty**—*CFS-9* - **HRQoL**—*EQ*-5D-5L - **Cognition**—*MiniMental State Examination (MMSE)* - **Medication safety**—*Safe Medication Assessment (SMA) and list of medications* -** Dependence**—*Activities of Daily Living (ADL-step)* - **Nutrition**—*Mini-Nutritional Assessment-Short Form (MNA-SF)*	**CFS-9** - Baseline - Post-op visit **EQ-5D-5L** - Baseline - Post-op visit - 12 months post-op **MMSE** - Baseline **SMA** and list of medications - Baseline - Post-op visit **ADL** - Baseline - Post-op visit **MNA-SF** - Baseline - Day of/day before surgery
Member of the project steering groups	- **Complications**—*Clavien-Dindo scale* - **Comorbidity**—*Charlson comorbidity index (CCI)*	**Complications** - Post-op visit **CCI** - Baseline - Post-op visit

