#### Comprehensive geriatric assessment and care

The team conducting the CGA and care intervention in the trial consists of internal medicine physicians with geriatric profiling, study nurses, physiotherapists (and/or occupational therapists) and dieticians. The team works in close contact with the colorectal surgeons at the clinic. During the day of interventions, each patient is individually assessed by one member of each profession (Fig. 1).

The multimodal concept of comprehensive geriatric assessment and care is considered best practice when treating frail elderly patients [30, 37]. The multiprofessional and team-based examinations and assessments of the elderly individual identify both problems and resources in the elderly population and the assessments should lay the grounds for recommended treatment and follow-up. The use of CGA enables underlying unidentified conditions and problems to be identified and, if needed, specifically targeted, optimized and treated [38, 39]. Considering sarcopenia and nutritional problems being highly present amongst the frail elderly, physiotherapists (and/or occupational therapists) and dieticians are important members of the CGA and care team. A geriatric assessment, especially with a focus on medications, including risks of polypharmacy, inappropriate medications and ADRs, is also crucial [30, 40, 41].

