#### Outcomes and measurements

*Hospital stays and discharge destination*, data regarding the length of hospital stay, total number of hospital days within 3 months after discharge, discharge destination and use of home help services and 30-day readmission rates for all participants is collected from patient medical records.*Dependence*, evaluation of the level of independence/dependence in an elderly individual is of great importance for example when establishing the need of home help services or other assistance. This is assessed using the activities of daily living (ADL)-staircase, which is a validated and commonly used instrument. The screening results in a score from 0 to 9, where 0 is completely independent and 9 is completely dependent [42, 43]. A clinically significant change is defined as a change of minimum 1 step in any direction on the ADL-staircase. ADL-function is assessed at baseline and at post-op visit (approximately 2 months post-surgery). The patients are assessed by a physiotherapist or a study nurse at baseline and follow-up.*Physical function*, the physiotherapists are also using hand grip strength (HGS) and six-minute walk test (6MWT) to make an overall assessment of the patient’s physical status to establish individual recommendations on physical activity and exercise. Both HGS and 6MWT have previously been used in assessments of frail elderly patients [44, 45]. The tests are performed at baseline and not at follow-up and are only conducted on patients in the intervention group as part of the CGA and care intervention.*Nutrition*, malnutrition is common in the elderly population, especially if hospitalized, living in nursing facility or having home help services. Malnutrition is often unrecognized if not specifically targeted. The Mini-Nutritional Assessment-Short Form (MNA-SF) is a validated instrument for nutritional screening in frail elderly individuals. It renders a score which places the patients in one of three groups: normal nutritional status, at risk of malnutrition or malnourished [46, 47]. A clinically significant change is defined as a change in group classification. The patients in the intervention group are screened by a dietician at baseline and by a ward nurse or a dietician at the day of/day before surgery. The patients in the control group are screened by a study nurse at both measurements.*Medication safety*, polypharmacy and the use of potentially inappropriate medications is a growing issue in the elderly population. There is often a need of reviewing and altering an elderly individual’s prescribed medications to reduce the risk of adverse drug reactions and to enable beneficial pharmacological treatments [48–50]. The Safe Medication Assessment (SMA), including a review of the current list of medications [51], is used as a basis for assessing the individual patient’s medications in the trial. The instrument renders a score of 0–30, where a higher score indicates a safer treatment. A clinically significant change is defined as a shift of minimum 1 point in either direction. The questionnaire is filled out by a study nurse at baseline and at revisit, for all participants. To identify adverse drug reactions (ADRs), underuse of evidence-based drug therapy and effects of inappropriate medications, scoring scales [49, 50] and clinical judgements based on medical records will be used. These judgements will be retrospectively performed by senior clinicians [52].*Cognition*, a decline in cognitive function is naturally present in the ageing process. Some elderly individuals are experiencing a more pronounced decline, resulting in cognitive impairment or dementia [53]. In the trial, the Mini-Mental State Examination (MMSE) is used as a screening instrument of cognitive function at baseline. It is a validated and reliable assessment tool in screening for cognitive impairment [54]. The screening is performed by a study nurse at baseline for all participants, but the measurement is not done at follow-up.*Frailty* is an independent risk factor of adverse health outcomes and death [21] and also a predictor of increased hospital and health care costs [25]. The degree of frailty is assessed using the Clinical Frailty Scale (CFS-9). The scale ranges from 1, “very fit”, to 9, “terminally ill”. The scale has been validated and proven to be of prognostic value in clinical practice [26, 55, 56]. The estimates are performed by a study nurse at baseline and at revisit, for all participants. A clinically relevant change is defined as a shift of minimum 1 step on the scale. During the initial phase of the trial’s recruitment, a revision of the CFS-9 scale was made, including minor adjustments in the description of the different levels of frailty [57]. Before the updated version (v 2.0) was put into use, a new application to the Swedish Ethical Review Authority was made and was approved on 2021-05-31.*Complications*, postoperative complications are common in elderly patients undergoing colorectal cancer surgery. The complications can result in additional treatments, reoperations, the need of intensive care and death [7, 8]. The Clavien-Dindo classification is a validated and clinically relevant instrument for identifying and grading adverse postoperative events [58]. The postoperative complications are assessed by a physician based on data from the medical records at the time of revisit, for all participants.*Comorbidity*, the patient’s comorbidity is valued through the Charlson comorbidity index (CCI). The instrument is used to assess the total burden of disease and predicts a 10-year mortality for a patient, by using 19 categories of comorbidities. Each condition is given a grade of 1, 2, 3 or 6, based on the risk of death associated with the specific comorbidity [59, 60]. The CCI index estimate will be performed by a physician, based on data from the medical records at baseline and at revisit, for all participants.*Health-related quality of life (HRQoL)*. The instrument EuroQoL-5D-5L (EQ-5D-5L) is used to assess HRQoL in the trial. The tool consists of a questionnaire containing five health dimensions with five response levels and of a visual analogue scale (VAS) where the patient estimates their own overall current health. Each estimated score is represented by an index value which is derived from a pre-defined value set [61, 62]. The assessments are overseen by a study nurse at baseline and at follow-up (2 and 12 months), for all participants.*Health economical calculations*. A health care system perspective will be applied including hospital and primary care. Cost-effectiveness will be analysed based on mortality and HRQoL data (quality-adjusted life years [QALYs]) and costs of hospital care and primary care at baseline, 2 and 12 months post-surgery. An incremental cost-effectiveness ratio (ICER) is calculated regarding cost/QALY gained. QALYs are calculated by multiplying the health state value with the patient’s survival time at 12 months; see also the “Statistical methods for primary and secondary outcomes” section. Data regarding health care costs will be collected and documented for all participants at 2 months and 12 months from baseline. Hospital costs will be obtained from the Swedish Cost-per-Patient database [63] and from hospital-specific administrative systems. Primary health care costs will be collected from the administrative regional health care database in Västra Götalandregion (VEGA) [64] and by the use of models and actual health care contacts.*Mortality*, mortality data will be extracted from patient medical records and cross-checked against the Swedish Population Registry regarding all participants at 2, 3 and 12 months from baseline.

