### Data management {19}

Each participant will be dealt a study number which further is used for identification. A specific key file is created for the identification, where personal identity numbers and study numbers are stored. This key file will only be kept at a hospital computer belonging to the local principal investigator. All examination results and medical considerations are documented in the medical chart. This is protected by the Swedish Law of Secrecy and Public Access. A CRF for each patient and all entered screening instruments (Tables 1 and 2) are obtained and held in a project-specific database and in patient-specific study binders.

There is no double data entry. Members of the steering committee intermittently conduct internal monitoring where the quality of entered study data is assessed. Likewise, an assessment of adherence to the protocol is conducted during these meetings. Adherence to the individual recommendations made by the health care professionals during the intervention is assessed during the weekly follow-up meetings (see item 11c).

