## Statistical methods

### Statistical methods for primary and secondary outcomes {20a}

The primary analysis will be performed according to “intention to treat”. As a secondary analysis, a per-protocol analysis will be made. The dataset will be closed, an analysis plan will be made and a multivariate analysis with relevant confounding factors will be performed.

QALYs are calculated by multiplying the health care state with the patient’s survival time at 12 months. The HRQoL is considered linear between 2 values (index and 12-month follow-up). If a person dies during follow-up, the HRQoL at index is carried forward to the time of death. If only HRQoL at index is available (missing data at the 12-month follow-up), the score is carried forward, and, conversely, if only the 12-month follow-up score is available (i.e. data missing at index), this score is carried backward to the index. If a person dies during the index care episode, the QALY is set to 0. Adjusted data regarding costs and effects might be used in the cost-effectiveness analysis. Adjustments are done for age, sex and CCI.

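### The Charlson index named for adjusting costs and effects is scored after randomisation in the CGA arm and by different roles in the two arms, so allocation can change the covariate

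*Protocol article*

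**What the plan says.** **Use of CCI.** Section {20a} says of the health-economic analysis: "Adjusted data regarding costs and effects might be used in the cost-effectiveness analysis". The next sentence gives the covariates: "Adjustments are done for age, sex and CCI". It does not say which CCI measurement is meant. For the clinical outcomes the same section says only that "a multivariate analysis with relevant confounding factors will be performed", without naming the factors. Section {20b} adds adjusted logistic and Cox models, again without a covariate list.

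**Who scores it, and when.** Table 1 places CCI for the intervention arm under the internal medicine physician, at baseline and at the post-operative visit. On timing, the Intervention group section says: "As soon as a patient has been randomized to the intervention group, they are scheduled for an" intervention day, on which that physician sees the patient. Table 2 gives the control arm's CCI, at the same two nominal time points, to a "Member of the project steering groups". The Comorbidity paragraph under Outcomes and measurements describes one procedure for everyone: "The CCI index estimate will be performed by a physician, based on data from the medical records at baseline and at revisit".

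**What reaches the record.** On the intervention itself the protocol says: "The use of CGA enables underlying unidentified conditions and problems to be identified". Data management {19} says: "All examination results and medical considerations are documented in the medical chart".

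**The concern.** A baseline covariate is safe to adjust for when allocation cannot have influenced its value. Here it can. The intervention includes a diagnostic work-up, its findings are charted, the chart is the source of the score, and in that arm a member of the team delivering the intervention does the scoring. The same patient could receive a different CCI depending on the envelope drawn.

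If CGA adds recorded diagnoses in one arm only, that arm looks sicker than it is. The model then credits the intervention with outcomes better than its apparent comorbidity predicts: adjusted QALYs move up and, if cost rises with CCI, the adjusted cost difference moves down. Cost-effectiveness is a listed secondary endpoint, so a shift in the adjusted incremental ratio would matter to readers. A revisit CCI would be worse in principle, because it is measured after both the intervention and surgery.

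**Working it through.** **1. Is the covariate open to influence by allocation?** Side by side:

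| | Intervention arm | Control arm |
|---|---|---|
| Scorer (Tables 1, 2) | CGA team physician | Steering group member |
| Timing of nominal baseline | Physician seen on the intervention day, after randomisation | CCI date not fixed; ward-staff instruments are done at admission, also after randomisation |
| Chart content by then | May include CGA findings | Standard work-up only |
| Cut-off at randomisation | None stated | None stated |

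The answer is yes. The common source in the Comorbidity paragraph does not change it, since only one arm's chart contains a CGA work-up.

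**2. The plan's own figures.** There is none on CCI or its adjustment. The 170 per arm enters below only as a sample size. It is reproduced closely: 15% v 5%, two-sided 0.05, 80% power with continuity correction gives 160, and 160/0.95 = 168.4, so 169.

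**3. Illustrative size.** Let d be the mean extra CCI points recorded in the intervention arm, b the log odds of death per point and k the utility lost per point. With no true effect:

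- adjusted odds ratio ≈ exp(−b·d)
- spurious utility gain ≈ k·d
- cost shift = −(cost per point)·d; no cost slope is available, so no value is given

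Assumed, not from the documents: mean CCI 2.5, odds ratio per point 1.2 or 1.4 (b = 0.182 or 0.336), k = 0.04, d from 0 to 1. The 15% mortality is the plan's control rate. The simulation used 300,000 per arm.

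| d | exp(−b·d), OR 1.2 / 1.4 | Simulated OR, 1.2 / 1.4 | k·d | Simulated utility gain |
|---|---|---|---|---|
| 0 | 1.00 / 1.00 | 1.00 / 0.99 | 0 | about 0 |
| 0.1 | 0.98 / 0.97 | 0.98 / 0.96 | 0.004 | 0.004 |
| 0.3 | 0.95 / 0.90 | 0.95 / 0.90 | 0.012 | 0.009 to 0.011 |
| 0.5 | 0.91 / 0.85 | 0.92 / 0.84 | 0.020 | 0.017 |
| 1.0 | 0.83 / 0.71 | 0.85 / 0.74 | 0.040 | 0.032 |

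The simulated utility gains are a little smaller than k·d, as expected when the extra points add noise to the covariate and dilute its slope. A gain of 0.01 held over the 12-month horizon is 0.01 QALY.

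For a mortality model with CCI at 170 per arm (1,500 repeats), the two-sided type I error was about 4% (OR 1.2, d = 0.3), 6% (OR 1.4, d = 0.3), 8% (OR 1.4, d = 0.5) and 14% (OR 1.4, d = 1.0). Simulation error is 0.6 to 0.9 percentage points.

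**4. The sign can reverse.** If control charts were the fuller ones at scoring, d is negative. At d = −0.3 the formula gives exp(0.182 × 0.3) = 1.06 to exp(0.336 × 0.3) = 1.11 for the odds ratio, and 0.04 × (−0.3) = −0.012 for utility, against the intervention.

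**5. After the fix.** With the same scoring in both arms d = 0. The simulation then returns odds ratios of 0.99 to 1.00 and a utility difference of about 0.

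**The case against.** A reader might infer that the trial's main result is biased in favour of CGA. The documents do not support that, for these reasons:

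- **Target.** CCI is named only for a cost-effectiveness adjustment that may or may not be made. It is not named for the mortality analysis, whose confounders are unspecified and can properly be left to an analysis plan. The odds ratios above apply only if CCI is chosen there.
- **Direction.** Standard care gives everyone a further surgical appointment and a pre-anaesthetic assessment, with cardiac or lung referral and tests where needed. If control CCI is scored around admission, those results may already be charted, whereas the intervention day may precede them.
- **Size.** The physician's additional evaluations in Table 1 are a medication review and an overall assessment with blood pressure and ECG. Nothing shows that CGA adds diagnoses in the 19 weighted Charlson categories, or how many points.
- **Common procedure.** The Comorbidity paragraph specifies a physician and the medical record for all participants. The case report forms, not shown here, may fix a scoring date.

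The first three points stand and limit the claim. The fourth narrows the asymmetry without removing it: the source is shared in name, but its content depends on allocation, and Tables 1 and 2 still name different scorers. Nor is this just detail left to an analysis plan, because the protocol itself names the covariate and sets an arm-specific way of scoring it.

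**Conclusion.** The point holds for the adjusted cost-effectiveness analysis, and conditionally for any other adjusted model that includes CCI. The covariate is scored after randomisation in the intervention arm, by different roles in the two arms, from a record the intervention can alter, without a cut-off and without saying which measurement is used. Bias is possible, but its net direction and size cannot be derived from the documents. If the only asymmetry is extra CGA diagnoses, it favours the intervention and is small unless several tenths of a point are added: about 0.01 to 0.017 in utility at 0.3 to 0.5 points, under the assumed slope of 0.04 per point. The unadjusted intention-to-treat comparison of 90-day mortality does not use CCI and is untouched.

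**What to change.** State in section {20a} that the adjusting CCI is the baseline score, limited in both arms to diagnoses recorded up to the date of randomisation and scored by the same physician role with CGA notes excluded. State also that neither the revisit CCI nor the CGA physician's own CCI is used as a covariate; the latter can remain a clinical tool. Reconcile Tables 1 and 2 with the Comorbidity paragraph so that all three name the same scorer, source and date.

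The cost is a date limit on a chart review already planned, and a small amount of rescoring from dated records for the roughly 50 of 340 patients included when the article was written, plus any since. No visits or procedures are added, and the sample size does not change.

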### Interim analyses {21b}

There are no planned interim analyses or stopping guidelines.

### Methods for additional analyses (e.g. subgroup analyses) {20b}

Data will be analysed according to the Intention-to-treat (ITT) principle. Subgroup analyses and sensitivity analyses are planned according to secondary aims, as are adjusted analyses using multiple logistic regression/Cox regression.

### Methods in analysis to handle protocol non-adherence and any statistical methods to handle missing data {20c}

The intention-to-treat (ITT) principle will be applied.

### Plans to give access to the full protocol, participant-level data and statistical code {31c}

The study protocol is available at ClinicalTrials.gov and at researchweb.org/is/vgr. The datasets analysed during the current study and statistical code are available from the corresponding author on reasonable request.

## Oversight and monitoring

### Composition of the coordinating Centre and trial steering committee {5d}

The trial has no separate steering committee, the trialists, [name] (principal investigator), [name] and [name], act as the steering committee.

### Composition of the data monitoring committee, its role and reporting structure {21a}

A data monitoring committee was not considered as this is regarded a low-risk intervention.

